## 232 **5.0 Statistical Analysis and Endpoints**

### 233 **5.1 Sample Size:**

234 This randomized control trial will aim to prospectively enroll 520 patients who have  
 235 received a positive confirmed diagnosis of coronavirus 2019. All patients will be followed for 28  
 236 days to review vital status, hospitalizations, emergency room visits, and need for additional  
 237 treatment. We assumed the standard of care group will have a 50% reduction of symptom  
 238 severity in approximately  $6 \pm 3$  days, and that at least one of the other 3 study groups will reach a  
 239 50% reduction in  $5 \pm 3$  days. When the sample size in each of the 4 groups is 130, a one-way  
 240 analysis of variance will have 80% power (2-sided alpha of 0.05) to detect a difference in means  
 241 characterized by a variance of means, V, of 0.188, assuming that the common standard deviation  
 242 is 3 days. Our study aims to enroll 520 patients to account for study drop out as well.

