## **2.0 Study Design, Objective, and Clinical Endpoints**

This is a prospective, randomized study which plans to enroll 520 patients with a principal diagnosis of COVID-2019, managed in an outpatient setting, who presented after being sent by a healthcare provider to get tested and receive a PCR-assay based confirmed diagnosis of the disease. All patients who agree to participate in the study will answer a baseline questionnaire about their symptoms at the time of inclusion. Patients will then be randomized to one of 4 study arms. Patients in Arm A (n=130) will receive 8000 mg of vitamin C (to be taken divided over 2-3 times a day with meals) for 10 days after positive diagnosis. Patients in Arm B (n=130) will receive zinc gluconate 50 mg for 10 days, to be taken at bedtime, after positive diagnosis. Patients in Arm C (n=130) will receive 8000 mg of vitamin C (to be taken divided over 2-3 times a day with meals) and zinc gluconate 50 mg for 10 days (taken at bedtime). Patients in Arm D (n=130) will not receive any of the study medications and continue on standard of care.

Patients will then track their symptoms daily from day 0 to day 28 answering 12 basic questions on illness severity. Symptom assessment tools will be completed by patients daily either electronically or on paper. For those completing the tool electronically a tool will be emailed to the patient daily via RedCap. For those completing the tool on paper a 28 day paper assessment tool will be provided to the patient at the time of consent via email/courier/text/express mail. For those patients completing a paper tool, a research staff member will contact the patient daily via phone call to obtain their daily assessment scores. Study team members will call patients at days 7, 14, 21, and day 28 of the study period to obtain information regarding hospitalizations, ER visits, additional medications prescribed by a healthcare provider

or over the counter, and any side effects from the study supplements that the patient could have experienced. Study team members may also call patients if non-compliance with completion of the daily symptom assessment tool.

Patients seen in the Emergency Department (ER) during the course of study participation will continue to take study supplement(s) (if within the initial 10 days) and continue daily symptom assessments as above.

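### Section 5.1 says that enrolling 520 patients covers drop-out, but 520 is exactly the 4 x 130 analysed patients behind the 80% power, so the allowance is zero

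*Protocol*

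**What the plan says.** The protocol's power statement is in section 5.1. It opens with the enrolment target: "This randomized control trial will aim to prospectively enroll 520 patients who have". It assumes that the standard-of-care group takes about 6 days (SD 3) to a 50% reduction in symptom severity and that at least one of the other three groups takes 5 days (SD 3). The power claim follows: "When the sample size in each of the 4 groups is 130, a one-way" "analysis of variance will have 80% power (2-sided alpha of 0.05) to detect a difference in means" "characterized by a variance of means, V, of 0.188, assuming that the common standard deviation" is 3 days. The paragraph closes with: "Our study aims to enroll 520 patients to account for study drop out as well".

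The other places agree on the count. The synopsis lists 520 subjects. Section 2.0 describes a study "which plans to enroll 520 patients with a principal diagnosis of COVID-2019" and puts 130 in each of Arms A to D; for the control arm, for example: "Patients in Arm D (n=130) will not receive any of the study medications". The protocol gives neither an expected drop-out rate nor an evaluable number below 130 per arm.

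**The concern.** A drop-out allowance is the difference between the number enrolled and the number the power calculation needs. Here the two numbers are the same, so the closing sentence of section 5.1 claims a reserve that does not exist.

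The 80% is the only power figure in the document. A reader who meets a null result would take it to come from a trial whose 80% power had been protected against attrition. The primary endpoint is built from daily scores reported by patients at home, and section 2.0 itself foresees calls to patients who do not complete the tool. Some loss is therefore a reasonable planning assumption, and the sentence shows that the sponsor expected it.

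**Working it through.** **Inputs, all from section 5.1:** k = 4 groups; n = 130 per group; variance of means V = 0.188; common SD = 3 days; alpha = 0.05; stated power 80%. Drop-out rate: none given.

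**Step 1. Count.** 4 x 130 = 520. Enrolled minus required = 520 - 520 = 0.

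**Step 2. Where V comes from.** Take means of 6, 6, 6 and 5 days. The grand mean is 5.75, and the variance with divisor 4 is (3 x 0.25² + 0.75²)/4 = 0.75/4 = 0.1875, which rounds to 0.188. Means of 6, 5, 5 and 5 give the same value. The stated V therefore fits the stated means.

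**Step 3. Reproduce the 80%.** The power of the overall F test is the probability that a noncentral F variable with k - 1 and k(n - 1) degrees of freedom, and noncentrality n·k·V/SD², exceeds the central F critical value.

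- Noncentrality: 130 x 4 x 0.188/9 = 10.86.
- Degrees of freedom: 3 and 4 x 129 = 516; critical value 2.62.
- Power: 79.5% (79.4% with V = 0.1875).

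The plan's 80% is reproduced to rounding, with all 520 patients analysed.

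**Step 4. Power of 520 enrolled when some supply no primary endpoint.** The same formula is used with n = 130(1 - d). The loss rates d are assumptions. Losses are taken as equal across arms, and a fractional n is kept.

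| Loss d | Evaluable per arm | Noncentrality | Power |
|---|---|---|---|
| 0 | 130 | 10.86 | 79.5% |
| 1 patient per arm | 129 | 10.78 | 79.2% |
| 4 per arm (about 3%) | 126 | 10.53 | 78.1% |
| 5% | 123.5 | 10.32 | 77.2% |
| 10% | 117 | 9.78 | 74.7% |
| 15% | 110.5 | 9.23 | 71.9% |
| 20% | 104 | 8.69 | 69.0% |

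**Step 5. What a real allowance would look like.** Keeping 130 evaluable per arm requires 130/(1 - d) enrolled per arm. At 5% this is 130/0.95 = 136.8, so 137 per arm and 548 in total. At 10% it is 130/0.90 = 144.4, so 145 per arm and 580 in total. Neither number, nor anything like it, appears in the protocol.

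**The case against.** The strongest case on the other side concedes the contradiction and disputes how far it reaches. Most of it stands.

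- *A reader might infer that the design does not have 80% power at all, because an exact 80% first appears at 132 per arm (528 in total).* The documents do not support that as a separate error. A figure of 79.5% rounds to 80%, and the half point is immaterial.
- *A reader might infer that the power claim fails as soon as anyone is lost.* It does not in any useful sense: power is still 78.1% with 126 evaluable per arm.
- *A reader might infer that loss of primary data is built in, because section 2.0 releases admitted patients from tracking.* That passage says only that tracking is no longer required. It does not exclude these patients from the analysis, and admission may come after the endpoint has been reached. No admission rate is given, and the handling of such patients may be set out in an analysis plan that is not shown. It adds no quantity here.
- *Drop-out is not the same as loss of the primary endpoint.* This is right. The endpoint is expected at about 5 to 6 days, counted from peak score, while tracking runs to day 28. A patient who stops after reaching the 50% reduction has already supplied it and is not lost. Daily calls to paper users and calls for non-compliance also limit the loss. The relevant rate may be well below overall drop-out, and nothing in the protocol points to 20%.
- *The size depends on the pattern of means.* This is also right. With two arms at 6 days and two at 5, V = 0.25 and power is 90.4% with no loss, 86.8% at 10% loss and 82.1% at 20%. With means of 6, 5.5, 5.5 and 5, V = 0.125 and power is only 60.1% before any loss. The table applies to the V that the protocol chose.

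None of this makes the drop-out sentence true. Nor is it a detail that can be left to an analysis plan: section 5.1 makes a positive claim that its own arithmetic contradicts.

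**Conclusion.** The point holds in a limited form. Section 5.1 claims a drop-out allowance, and the allowance is zero. The 80% power is correct for 130 analysed patients per arm and for nothing less.

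The practical shortfall is trivial for a few losses and material from about 5% of patients without a primary endpoint. If 10% were lost, power would be 74.7%, which means a type II error of about 25% where about 20% was planned. These figures rest on V = 0.188, SD 3 days, equal losses across arms and loss rates assumed here, since the protocol states none.

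This is a misstatement of planning power that should be corrected. It does not touch the endpoint, the test, the allocation or the type I error.

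**What to change.** Delete the drop-out sentence in section 5.1 and replace it with text along these lines: *With 130 evaluable patients per arm (520 in total), the one-way ANOVA has about 80% power (79.5%) for V = 0.188 and SD 3 days. No allowance for drop-out is included. If 10% of the 520 enrolled patients do not supply the primary endpoint (117 evaluable per arm), power is about 75%.* The 10% is an example; the sponsor should put in the loss of the primary endpoint that it expects and give the matching power.

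The cost is one or two sentences and a slightly less favourable power figure. Enrolment need not rise. If the sponsor would rather keep the claim of an allowance, it must state a rate d and enrol 130/(1 - d) per arm, for example 580 in total at 10%.

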### 243 **5.2 Primary Endpoints**

244 The primary endpoint will be the number of days required to reach a 50% reduction in the  
 245 symptom severity score from peak symptom score.

### 246 **5.3 Secondary Endpoints**

247 Additional endpoints to be considered include:

248 A) Number of days required to reach a total score of 0

B) Individual severity of illness scores (fever, cough, shortness of breath, fatigue)

C) Cumulative severity score at day 5 of the study

D) Emergency room visits

E) Hospitalizations

F) Adjunctive prescribed medications

G) Side effects of supplementation

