(none of these additional supplements). These supplements will be given to patients for a duration of ten days as a part of the study. Patients will be asked to track their symptoms of systemic illness on a daily basis.(Appendix A: Symptom Assessment Tool). We will track 12 symptoms on a scale of 0-3 as follows: A) Temperature Scale (if patient has a thermometer): 0 =  $\leq 98.6$ , 1 =  $> 98.6 - 100.6$ , 2 =  $> 100.6 - 102.6$ , 3 =  $> 102.6$ ; If no thermometer: 0= No fever & no chills, 1= No fever & chills, 2= Fever & no chills, 3= Fever & chills B) Cough Scale: 0 = no cough, 1 = mild, 2 = moderate, 3 = severe C) Shortness of breath: 0 = no shortness of breath, 1 = with moderate intensity exercise 2 = with walking on flat surface 3 = short of breath with getting dressed or daily activities D) Fatigue: 0 = No fatigue/energetic, 1=mild fatigue, 2=moderate fatigue, 3=severe fatigue E) Muscle or body aches: 0 = No muscle or body aches, 1=mild muscle or body aches, 2=moderate muscle or body aches, 3=severe muscle or body aches. F) Headache: 0 = No headache, 1=mild headache, 2=moderate headache, 3=severe headache G) New loss of taste: 0 = No loss of taste, 1=mild loss of taste, 2=moderate loss of taste, 3=severe loss of taste H) New loss of smell: 0 = No loss of smell, 1=mild loss of smell, 2=moderate loss of smell, 3=severe loss of smell I) Congestion or runny nose: 0 = No congestion or runny nose, 1=mild congestion or runny nose, 2=moderate congestion or runny nose, 3=severe congestion or runny nose J) Nausea: 0 = No nausea, 1=mild nausea, 2=moderate nausea, 3=severe nausea K) Vomiting: 0 = No vomiting, 1=mild vomiting, 2=moderate vomiting, 3=severe vomiting L) Diarrhea: 0 = No diarrhea, 1=mild diarrhea, 2=moderate diarrhea, 3=severe diarrhea. Each patient will have a composite score ranging from 0-12/day. The tracking will continue for the 28 days of study participation for each subject. They will also be asked to complete a questionnaire at the beginning of study period, day 7, day 14, day 21 and day 28. The purpose of the

questionnaire is to assess whether patient received additional medications/ supplements, sought treatment at emergency rooms or were hospitalized, or experienced side effects from the study supplements.

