The primary clinical endpoint is the number of days required to reach a 50 percent reduction in the cumulative 0-36 score from the four symptom categories. For secondary endpoints we will assess a) the number of days required to reach a score of 0 b) total composite score at day 5 of the supplementation, c) differences in emergency room visits and d) differences in hospitalizations e) differences in severity of symptoms between study arms f) differences in number of patients who were prescribed adjunctive medications for their diagnosis, and g) differences in number of patients in study arms who experienced side effects from the supplements.

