Patients admitted to the hospital during the course of study participation will no longer be required to continue study supplementation nor track their daily symptoms.

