## **5.4 Analytical Plan**

Descriptive statistics will be generated for all baseline patient characteristics, complications, and endpoints. Frequency counts and percentages will be used to summarize binary and categorical data. Continuous data will be summarized using means  $\pm$  standard deviation, median and interquartile range, and minimum/maximum values. ANOVA tests will be used to describe the difference in number of days to a 50% reduction on the symptom severity score between the four groups. All pairwise comparisons will be generated and adjusted for multiple comparisons using the Tukey method.

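### Days to a total score of 0 (secondary endpoint A) can be observed only to day 28, yet the only summary the protocol gives for a numeric endpoint has no place for patients still symptomatic then

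*Protocol*

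**What the plan says.** Protocol section 5.3 A names the endpoint as the "Number of days required to reach a total score of 0"; section 1.1 lists it too, as "the number of days required to reach a score of 0". The score is demanding. Section 1.1 states "We will track 12 symptoms on a scale of 0-3 as follows", so a total of 0 needs all 12 items at 0 on the same day.

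Observation is limited in two ways. Section 1.1 says "The tracking will continue for the 28 days of study participation for each subject". Section 2.0 adds that patients admitted to hospital "will no longer be required to continue study supplementation nor track their daily symptoms".

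Section 5.4 opens with a commitment that covers every endpoint: "Descriptive statistics will be generated for all baseline patient characteristics, complications, and endpoints". It then sorts data into two kinds. Binary and categorical data get counts and percentages. For the rest, "Continuous data will be summarized using means" with standard deviation, plus median, interquartile range, minimum and maximum. ANOVA with Tukey-adjusted pairwise comparisons is named only for days to a 50% reduction. No between-arm test is named for A, and the protocol contains no censoring rule, assigned value or time-to-event method for it.

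**The concern.** A day count is numeric, so under section 5.4 it falls to the mean and median. A fully compliant outpatient whose score is still above 0 on day 28 has no day count to enter. A mean of the available counts is then a mean among resolvers, and the missing values are by construction the longest ones.

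Two things follow. Each arm's time to symptom freedom looks too short. And because a slower arm has more unresolved patients, it loses more of its long values, so the difference between arms tends to shrink. An arm with more patients still ill at day 28 can look much like an arm with fewer. In a trial about symptom duration, complete resolution is the first secondary endpoint listed, so its summary should not depend on who happened to finish within the window.

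**Working it through.** **The plan's own figure.** Section 5.1 gives 80% power for the primary endpoint with 130 per arm, variance of means 0.188, SD 3 and two-sided alpha 0.05. The noncentrality is 4 × 130 × 0.188 / 9 = 10.86 with 3 and 516 degrees of freedom, which gives power 0.795. This reproduces, but it concerns days to 50% reduction and does not bear on A.

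**The primary endpoint is not the problem.** Section 5.1 says "We assumed the standard of care group will have a 50% reduction of symptom" severity in about 6 ± 3 days. Day 28 is (28 − 6)/3 = 7.3 SDs above that mean. The share beyond day 28 is below 0.01% under a normal or a gamma distribution.

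**What is assumed for A.** The protocol gives no share unresolved at day 28, no peak score and no curve shape. I take time to 50% reduction, h, as gamma with mean 6 (standard of care) or 5 (supplement) and SD 3, with the peak on day 0, and vary the shape of decline.

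*Linear decline.* Time to 0 = 2h, so a patient is unresolved if h > 14. This gives 1.7% on standard of care and 1.2% on supplement. The true difference of 2.01 days appears as about 1.95 days among resolvers.

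*Exponential decline, score read as 0 once below 0.5.* Time to 0 = h × log2(peak / 0.5), rounded up to whole days (simulated):

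| Peak | Halvings | Unresolved at day 28, standard of care / supplement | True difference, days | Difference among resolvers, days | Lost |
|---|---|---|---|---|---|
| 4 | 3.00 | 13% / 9% | 3.0 | 2.4 | 21% |
| 8 | 4.00 | 31% / 21% | 4.0 | 2.5 | 39% |
| 12 | 4.58 | 42% / 29% | 4.6 | 2.4 | 47% |

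At peak 8 the standard-of-care mean of 24.5 days appears as 18.0, and the median of 23 appears as 18. A two-patient case shows the mechanism. With peak 8 and half-lives of 5 and 8 days, the score reaches 0 on day 5 × 4 = 20 and day 8 × 4 = 32. The first patient is counted, the second is not, and the mean is 20. Normal half-lives or a peak on day 3 raise the share unresolved, to as much as 57%.

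**Entering 28 instead.** At peak 8 the standard-of-care mean becomes 21.1 days against a true 24.5, and the difference 2.9 days against 4.0. This is better than dropping patients and is legitimate if labelled a 28-day restricted mean. Reported as the mean number of days to 0, it is still too short.

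**Direction under a different model.** Let recovery times themselves be exponential with a share c of controls unresolved at day 28. The rate is r = −ln(c)/28, the true mean is 1/r, and the mean among resolvers is 1/r − 28c/(1 − c). For c = 20% the true mean is 17.40 days and the resolver mean is 17.40 − 7.00 = 10.40. With a hazard ratio of 1.25, the true difference of 3.48 days shows as 0.81 among resolvers, while a 28-day restricted mean shows 1.86. These inputs are not tied to section 5.1, so they support the direction and not the size.

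**The case against.** The strongest reply is that the alleged error is never written. Section 5.3 lists A among endpoints to be considered, and section 5.4 neither labels A as continuous nor says that unresolved patients are left out. Entering 28, or ranking unresolved patients last, is equally compatible with the wording. With unresolved patients ranked last, the promised median could be read off in every gamma scenario above, since at most 42% are unresolved. A censoring rule for a secondary endpoint is also ordinary content for a statistical analysis plan that is not at hand.

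Much of this stands. A reader might infer that the protocol directs slow recoverers to be dropped. It does not; exclusion is only what a literal application produces. What remains is that section 5.4 does commit to descriptive statistics for all endpoints and offers one summary for numeric data, and that summary cannot be computed on every patient. The point is the method stated, not a missing detail.

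A reader might also infer a loss of around 40% of the treatment difference. That figure depends on exponential decline from a peak near 8. Linear decline, equally consistent with section 5.1, removes nearly all of it.

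Finally, a reader might infer lost power. The protocol names no test for A and powers only the primary endpoint, so no planned power is lost. Even as illustration the contrast is mixed. At peak 8 with 130 per arm, a t-test has 75% power on resolvers against 78% on untruncated data, while a rank test has 72% on resolvers against 87% with everyone kept. Only the second pair shows a material cost of exclusion.

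**Conclusion.** The concern holds in a limited form. Endpoint A is a day count observed only to day 28, and the one summary that the protocol gives for numeric data leaves patients still symptomatic at day 28 without a value. Taken literally, it describes resolvers only, shortens apparent time to symptom freedom and tends to narrow differences between arms.

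The size cannot be settled from the document. Under the section 5.1 figures it runs from under 2% unresolved with almost no distortion (linear decline) to 13% to 42% or more unresolved on standard of care, with roughly 20% to 47% of the true difference lost (exponential decline, peaks 4 to 12). Both ends rest on assumed curve shapes, gamma times to 50% reduction and a peak on day 0.

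The primary endpoint is hardly touched. The distortion tends to understate a difference rather than create one. Severity: low to moderate.

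**What to change.** In sections 5.3 A and 5.4, define A as time to first total score of 0, censored at day 28 or at the last diary entry if earlier. Keep all randomised patients in the denominator. Report Kaplan-Meier medians with a log-rank test, or a 28-day restricted mean, together with the percentage who have reached 0 by day 28 in each arm. Do not give a mean among resolvers as the arm result.

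State separately how patients who stop tracking on hospital admission are counted in this analysis, for example as not resolved through day 28. Censoring them at their last diary entry would treat them as having the same prospects as patients who stayed at home, which is doubtful.

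The cost is a few sentences and standard procedures in the software already named in section 7.1; no new data or patients are needed. The downside is that reported times become longer and an arm's median may not be reached by day 28, in which case the percentage resolved carries the result.
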